## 2. OBJECTIVES

**Primary Objective:** At 2 years after surgery, what is the effect of a final follow up within 3 months combined with check-ups on demand (COD) compared to routine follow-up (RFU) within 3 months and at 1 year after total hip and knee arthroplasty (THA and TKA) on physical function (effectiveness) and clinical visits (implementation)?

**Secondary Objective(s):** At 2 years after surgery, what is the effect of a final follow up within 3 months combined with COD compared to RFU within 3 months and at 1 year after THA and TKA on complications, surgical interventions, quality of life (QoL), pain and costs.

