## **8. METHODS**

### **8.1 Study parameters/endpoints**

#### **8.1.1**

##### **Main study parameter/endpoint**

- Clinical: PROMIS physical function
- Process (healthcare consumption): number of clinical visits and X-rays

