### **10.1 Primary study parameter(s)**

PROMIS physical function will be presented as mean with standard deviation, assuming normality. Differences in PROMIS physical function between the RFU and COD groups will be compared using linear mixed models, with repeated measurements clustered within participants and participants clustered within hospitals (random intercepts). The intervention group (RFU vs. COD), baseline PROMIS physical function, and time points (12, 15, 18 and 24) will be included as fixed effects to determine the crude effect of the intervention at each time point, with the primary outcome at 24 months. Given the stepped wedge design, the duration of the intervention period differs between sites. Therefore “period” is also included as a fixed effect. To assess of the effect of COD might increase over a longer period of time, an interaction term (period \* intervention) will be tested for these possible time effects for the primary outcome.

For healthcare consumption, the percentage of patients who have had at least one clinical visit or X-ray 1 year after RFU or COD will be presented for each group. Additionally, the average number of visits and X-rays per patient will be reported.

A logistic generalized linear mixed model (GLMM) will be used to compare the presence or absence of visits/X-rays (yes/no per patient) between RFU and COD. A Poisson regression analysis will be performed to assess the average number of visits and X-rays per patient, adjusting for potential confounders. Interaction terms between the confounders and the intervention group will also be included to explore whether certain patient characteristics influence the differences in healthcare consumption between RFU and COD.

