### 10.4 Other study parameters

The additional study parameters, including patient characteristics, surgical characteristics, and postoperative characteristics, will be used to describe the study population and adjust for potential confounders. These variables will help account for potential baseline differences between groups, allowing for more accurate estimation of intervention effects. Patient characteristics, surgical characteristics, and postoperative characteristics will be presented as means and standard deviations for continuous variables, and frequencies and percentages for dichotomous variables. These characteristics will be used to describe the study population and adjust for potential confounders in the analysis. Including these variables in the model will help control for baseline differences between groups, thereby reducing bias and leading to more accurate and reliable estimates of the intervention effects.

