### 10.5 Exploratory analysis

As an exploratory analysis, we will assess subgroup effects on the primary outcomes of complications, clinical visits and X-rays. The GLMMs described above will be extended, by including interaction terms for age, gender, BMI, ASA-score, ethnicity, employment status, and educational level with the intervention in separate models.

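### Section 10.1 adds confounder-by-intervention interactions to the Poisson analysis of visits and X-rays without saying that the overall RFU–COD comparison comes from a model without them

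*Protocol*

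**What the plan says.** Section 8.1.1 lists as a main parameter "Process (healthcare consumption): number of clinical visits and X-rays". The primary objective in section 2 asks for the effect of COD against RFU on physical function and on clinical visits, that is, one overall contrast for each.

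Section 10.1 handles healthcare consumption in three ways: descriptive percentages and averages per group, a logistic mixed model for any visit or X-ray, and a model for the count. The last reads "A Poisson regression analysis will be performed to assess the average number of visits and X-rays per patient, adjusting for potential confounders". The sentence straight after it begins "Interaction terms between the confounders and the intervention group will also be included" and gives the purpose: "to explore whether certain patient characteristics influence the differences in healthcare consumption between RFU and COD". It names no separate model, no preceding main-effects step, no centring and no standardised contrast.

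Section 10.4 draws the confounders from the patient, surgical and postoperative characteristics, which "will be used to describe the study population and adjust for potential confounders". Section 10.5 describes an exploratory subgroup analysis that extends the GLMMs "by including interaction terms for age, gender, BMI, ASA-score, ethnicity, employment status, and educational level with the intervention in separate models". It does not mention the Poisson regression. The parallel Poisson analysis of secondary counts in section 10.2 carries no interaction terms.

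**The concern.** Once a regression contains products of the intervention with covariates, its intervention coefficient no longer summarises the difference between the groups. It describes the difference at one covariate pattern, which the coding fixes. With age in years and BMI in kg/m² entered as they stand, that pattern is a patient aged 0 with a BMI of 0, whereas section 4.2 admits only patients of 50 or older.

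The implementation half of the primary objective is at stake. If an analyst follows 10.1 to the letter and reports the intervention term from the fitted model, the reported rate ratio may answer a different question from the objective. It may also carry a confidence interval far wider than the data warrant. The protocol does not rule this out.

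**Working it through.** **The plan's own figures.** The protocol states no effect size, power or precision for visits or X-rays, so there is no figure on this point to reproduce. Its one design figure, for PROMIS in section 4.4, does reproduce: 2 × 9² × (1.960 + 1.282)² / 3² = 189.1, rounded up to 190 per group, and 190 / 0.76 = 250 at 24% loss. It has no bearing on the count model beyond giving group sizes.

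**Step 1: algebra, no assumptions needed.** Let G = 1 for COD and 0 for RFU, and let X be the confounders. The model as written is

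log E(Y) = a + bG + c′X + d′(G·X).

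The log rate ratio for a patient with covariates X is b + d′X. The coefficient b alone is the log rate ratio at X = 0. It represents the overall effect only if d = 0 or if X is coded so that zero is the average patient.

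**Step 2: how far b can move.** Assumed inputs, not in the protocol:
- Poisson counts, 250 per group, 300 replicates, no hospitals or periods.
- RFU mean about 1.4; rate ratio 0.50 at the average patient.
- Age mean 69, BMI mean 28, 25% in the higher ASA class, 62% women.
- Moderate interaction on the log scale: 0.10 per 10 years, 0.3 for ASA, 0.1 per 5 BMI units. Strong interaction: 0.2, 0.5 and 0.2.

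For moderate interaction the true value of b follows directly:
- Nothing centred: ln 0.50 − 0.10 × 6.9 − 0.3 × 0.25 − 0.1 × 5.6 = −0.693 − 0.690 − 0.075 − 0.560 = −2.018, a rate ratio of 0.13.
- Zero set at age 50 and BMI 25: −0.693 − 0.190 − 0.075 − 0.060 = −1.018, a rate ratio of 0.36.

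Simulated rate ratios, with the mean SE of the log rate ratio in the last column:

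| Model | No interaction | Moderate | Strong | SE |
|---|---|---|---|---|
| Main effects only | 0.50 | 0.52 | 0.54 | 0.09 |
| Interactions, nothing centred | 0.50 | 0.13 | 0.03 | 0.93 |
| Interactions, zero at age 50 and BMI 25 | 0.49 | 0.36 | 0.27 | 0.27 |
| Interactions, every covariate centred | 0.50 | 0.50 | 0.50 | 0.09 |
| Interaction model, standardised over the sample | 0.50 | 0.52 | 0.54 | not computed |

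The main-effects coefficient agrees with the standardised overall rate ratio in all three settings.

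**Step 3: precision with the covariates of 10.5.** Assumed: 190 per group, means of 1.5 (RFU) and 0.9 (COD), the seven characteristics of 10.5 with assumed distributions, and no clustering. Repeated runs gave these SEs for the log rate ratio:
- Main effects only: 0.097 to 0.098.
- All interactions, age and BMI centred, factors at reference: 0.23 to 0.24.
- All interactions, nothing centred: 0.97 to 1.09.
- All interactions, every covariate centred, including the factor indicators: 0.100.

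A 95% interval multiplies and divides the estimate by exp(1.96 × SE). That factor is about 1.22 at an SE of 0.10, 1.60 at 0.24 and 7.1 at 1.0.

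**The case against.** The best defence is the rest of the sentence. Its stated aim is to explore, and the word for addition suggests a further step after an adjusted Poisson analysis. It does not say that the interactions sit in the same model, and nowhere does the protocol say that the main result will be read from the intervention coefficient of an interaction model. This stands as a statement of likely intent. It does not settle the matter, because no main-effects step is named and the sentence is attached to the only model given for the count.

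The overall comparison also does not rest on this model alone. Section 10.1 reports group percentages and averages and fits a logistic mixed model to any visit or X-ray. That stands too, although the averages are unadjusted and the logistic model addresses a different quantity.

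The loss of precision depends on coding. With every covariate centred, the full interaction model loses almost nothing (0.100 against 0.098), and standardisation recovers the overall ratio. This is correct and limits the claim. The protocol specifies neither device.

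One could call the issue detail for the statistical analysis plan. Centring and model order are indeed such detail. The protocol does more than leave them open, however: it positively places the interactions in the analysis of a main outcome.

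A reader might also infer that 10.1 contradicts 10.5. The text does not support that. Section 10.5 extends only the GLMMs and does not name the Poisson regression. The two sections treat similar terms differently, but for different models. For the same reason, simply deleting the sentence from 10.1 would lose effect modification for counts.

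**Conclusion.** The concern holds as a matter of specification. Section 10.1 adds covariate-by-intervention terms to the analysis of the count outcome and does not reserve the overall comparison for a model without them. That the intervention coefficient is then a conditional effect at covariate zero or reference level follows from the algebra and needs no assumption.

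The size does rest on assumptions: the contact rates, the covariate distributions, the strength of any interaction, and the absence of hospital and period effects. Under them the SE of the log rate ratio runs from about 0.10 (main effects only, or every covariate centred) through about 0.24 (age and BMI centred, factors at reference) to about 1.0 (nothing centred). Bias relative to the overall effect appears only if true interactions exist; the loss of precision under uncentred or reference coding appears even without them.

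It would be tempting to conclude that the trial's main process result is already the wrong quantity, or that its power falls by a known amount. Neither follows. The protocol does not say which coefficient will be reported, and the simulations contain no clustering, so they do not give this trial's power. The point is an ambiguity that should be closed before analysis.

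**What to change.** In 10.1, state that the overall rate ratio for visits and X-rays is estimated from the Poisson model with intervention, confounders and design terms (hospital and period, which 10.1 already names for PROMIS), and with no covariate-by-intervention interactions.

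Move the interaction sentence to 10.5. Extend 10.5, which now names only the GLMMs, so that it also covers the Poisson model, with the interactions fitted in separate exploratory models. The question of effect modification for counts is then kept.

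The cost is a few words in two sections. No data collection, sample size or other analysis changes.

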### **10.2 Secondary study parameter(s)**

For complications, surgical interventions, and additional healthcare consumption, the percentage of patients who have experienced each will be presented for each group.

Additionally, the total number of complications, interventions, and additional healthcare consumption per patient will be reported. Logistic GLMM will be used to compare the presence or absence of complications, surgical interventions, and additional healthcare consumption (yes/no per patient) between RFU and COD. A Poisson regression analysis will be performed to assess the total number of complications, interventions, and additional healthcare consumption per patient, adjusting for potential confounders.

Quality of life (EQ-5D-5L) and pain (NPRS) will be analysed using mixed models, with repeated measures clustered within participants and participants within hospitals (random intercepts). Intervention group (RFU vs. active COD vs. passive COD), baseline score, and time (15, 18 and 24 months) are included as fixed effects. Satisfaction (NSRS) will be analyzed using independent t test to compare the mean difference between the RFU and COD group.

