### 1. INTRODUCTION AND RATIONALE

Total Hip Arthroplasty (THA) and Total Knee Arthroplasty (TKA) are two of the most common procedures for patients suffering from osteoarthritis and other degenerative joint diseases. These surgeries are highly effective in reducing pain and improving mobility. In 2022, more than 36,700 THAs and 26,700 TKAs were implanted (1,2), with osteoarthritis being the primary indication in 86% and 97% of cases, respectively (3,4). Given the growing elderly population and rising demand for these surgeries, the need for optimized follow up care has become increasingly important.

Current clinical guidelines recommend routine follow up (RFU) for patients after THA and TKA, with an X-ray and clinical visit within 3 months post-surgery and again at 1 year (5,6). There is currently insufficient high-level evidence to support or challenge the continued use of routine follow-up. The current guidelines for RFU after THA and TKA are based on limited observational data, and randomized controlled trials (RCTs) in this area are rare. A recent NIHR report recommended eliminating RFU before 1 and 10 years in patients with well-functioning implants but did not address the cost-effectiveness or other outcomes relevant to patients associated with RFU 1 year after surgery (7).

Studies show that early follow-up up (FU) to 1 year after surgery results in 0–4.6% detected abnormalities (8,9), of which only a small proportion impacts clinical decision-making and requires additional treatment (10-13). Moreover, in patients indicated for revision surgery, >96.7% present with clinical symptoms such as pain or loss of function. This suggests that early RFU could be safely replaced by check-ups on demand (COD). Registry data also indicate that revisions are rare and typically preceded by symptoms (14-16), bringing the added value of routine follow-up into doubt. Clinical experience further supports the notion that the risk of missed complications is low for asymptomatic patients, which raises the question of whether RFU can be safely de-implemented.

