Despite this, eliminating RFU entirely is not without risks. The balance between reducing unnecessary healthcare resource use and ensuring patient safety requires careful consideration. Additionally, patients may find it reassuring to receive confirmation that everything is going well and that they can go back to normal activities, especially as many are not fully recovered at the clinical visit within 3 months post-surgery. Therefore, we suggest a final follow-up within 3 months and then offering COD, as requested by the patient or the healthcare provider (HCP).

The primary objective of this study is to assess whether RFU after THA and TKA can be safely replaced by COD, by comparing the cost-effectiveness of the two approaches 1 year after surgery. The HAKA trial will generate the high-quality evidence necessary to standardize care and guide future clinical practice.

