### **4.4 Sample size calculation**

We carefully considered the number of patients needed to obtain reliable estimates of the outcomes with the co-creating stakeholders and also asked orthopaedic surgeons for their opinion of convincing evidence. The agreed sample size is 250 patients per group. To provide a rough indication of the statistical power, we used the online power calculator tool available on Sealed Envelope (18). If there is truly no difference between COD and RFU, 190 patients (per intervention group) are required to be 90% sure that the lower limit of a one-sided 97.5% confidence interval will be above the non-inferiority limit of 3 on the PROMIS score with a standard deviation of 9. Anticipating 20-25% loss to follow up, we will include 250 patients per study intervention group (RFU and COD), thus a total of 500 THA and 500 TKA patients.

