## **10. STATISTICAL ANALYSIS**

All analyses will be performed separated for THA and TKA and will be performed using SPSS or R. Categorical data will be presented as numbers and percentages. Continuous variables will be presented by mean and standard deviation in case of a normal distribution. In case of non-normality, median and interquartile range will be given.

Missing data will be minimized as much as possible by contacting patients in case of incomplete questionnaires. After finalizing the database, the extent of missing data will be assessed. Mixed models will address missing data, and if necessary, multiple imputation will be employed, provided that the data are missing at random (20,21).

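### The trial asks whether RFU can be replaced safely, but the per-joint comparisons of complications and surgical interventions are too imprecise to show it; add a pooled hip-and-knee risk difference with its upper confidence limit

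*Protocol*

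**What the plan says.** - **Aim.** Protocol section 1 states the primary objective as to "assess whether RFU after THA and TKA can be safely replaced by COD, by comparing the cost-effectiveness of the two approaches". The Summary and section 11.4 both name missed complications as a risk of dropping the 1-year visit.
- **Status of the outcomes.** Section 2 makes the effect "on complications, surgical interventions, quality of life (QoL), pain and costs" a secondary objective, and section 8.1.2 lists complications and surgical interventions as secondary endpoints. Section 10.5 disagrees: "we will assess subgroup effects on the primary outcomes of complications, clinical visits and X-rays".
- **Analysis.** Section 10.2 plans percentages per group and then: "Logistic GLMM will be used to compare the presence or absence of complications, surgical interventions, and additional healthcare consumption (yes/no per patient"). It also plans a Poisson regression of the number of events, adjusted for confounders. Section 10 adds: "All analyses will be performed separated for THA and TKA".
- **Margin.** The one margin in the protocol is the "non-inferiority limit of 3 on the PROMIS score with a standard deviation of 9" in section 4.4. No tolerable excess, expected rate or reading rule is given for complications or surgical interventions.

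**The concern.** A claim of safe replacement is a claim that any excess of harm is small. Comparing two groups on a rare yes/no outcome does not answer that by itself, because with few events the comparison is likely to be inconclusive whether or not COD causes harm. The PROMIS margin does not fill the gap: it bounds a difference in mean function, not an event rate. Analysing each joint separately halves the number of events behind each estimate, for the outcomes where events are scarcest.

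Section 3 intends all centres to end up using COD. A reader of the results will want to know how large an excess of complications or re-operations the data still allow, and the plan does not lead to that statement.

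**Working it through.** **1. The plan's own figure.** Section 4.4 uses margin 3, SD 9, one-sided 2.5%, 90% power and a true difference of 0.
n = 2 × 9² × (1.960 + 1.282)² / 3² = 189.1, so 190 per group. Allowing for loss, 190/0.80 = 238 and 190/0.75 = 254, so 250 per group and joint is consistent. This figure concerns PROMIS only.

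**2. Power to detect a doubling of complications, per joint.**
Assumptions not in the protocol: control rate p, two-sided 5%, independent patients. Section 1 gives 0 to 4.6% for abnormalities detected at early follow-up. That is not a complication rate, so p is varied. Both 190 (the analysable number in section 4.4) and 250 (nobody lost) are shown.
The test is the likelihood-ratio test of the logistic group effect, rejecting when G² = 2 Σ O ln(O/E) > 3.84. Power sums Bin(x; n, p) × Bin(y; n, 2p) over all outcomes (x, y) that reject.

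| Control rate → doubled | Power, 190 per arm | Missed | Power, 250 per arm | Missed |
|---|---|---|---|---|
| 1% → 2% | 18% | 82% | 20% | 80% |
| 2% → 4% | 24% | 76% | 27% | 73% |
| 3% → 6% | 32% | 68% | 37% | 63% |
| 4.6% → 9.2% | 45% | 55% | 54% | 46% |
| 10% → 20% | 79% | 21% | 89% | 11% |

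Other tests are no kinder over 2% to 4.6%. The normal approximation gives power of 21% to 42% (190 per arm) and 26% to 53% (250). Fisher's exact test gives 12% to 35% and 18% to 47%.

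**3. What pooling the joints does to this test.** With 380 per arm (2 × 190), power for a doubling is 37%, 53% and 72% at 2%, 3% and 4.6%. That is better, but at 2% a doubling is still missed 63% of the time.

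**4. The upper limit on the risk difference.** Take equal true rates of p = 8/380 = 2.1%. Without period terms, the limit is 1.96 × √(2p(1−p)/n):
- per joint, n = 190: 1.96 × √(2 × 0.0206/190) = 2.9 points
- pooled, n = 380: 1.96 × √(2 × 0.0206/380) = 2.0 points

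Newcombe limits are +3.4 (4/190 in each arm) and +2.2 (8/380 in each arm).

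These ignore the stepped-wedge design. In Table 1 only January and February 2026 have RFU and COD centres including patients in the same month, so calendar time and intervention are strongly confounded. Using the Table 1 layout, a hospital random intercept with ICC 0 to 0.1 and a linear-scale approximation:

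| Calendar adjustment | Variance multiplier, pooled | Pooled limit (380) | Per-joint limit (190) |
|---|---|---|---|
| none | about 1 | about +2.0 | about +2.9 |
| linear trend | 4.4 to 5.0 | +4.3 to +4.6 | +6.0 to +6.3 |
| monthly effects | 9.4 to 10.4 | +6.2 to +6.6 | +8.8 to +9.2 |

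Under every adjustment pooling narrows the limit by about 30% (1 − 1/√2 = 29%). With about 16 events in all (8 per arm) and 14 monthly effects, a monthly logistic model may not be estimable.

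**The case against.** - **A reader might infer that a non-significant result will be reported as safety.** The protocol sets no such rule. Section 1 ties safe replacement to a cost-effectiveness comparison, and section 2 asks about an effect on complications as a secondary objective. This stands.
- **A reader might also infer that a two-sided difference test is the only inference and leaves no bound to read.** Section 10.2 states neither alpha nor sidedness, it also plans a Poisson model, and a logistic GLMM yields an odds ratio with an interval. Whether results are read from the interval or a p-value may be left to the SAP. This stands too.
- **The miss rate rests on an assumed control rate.** The complication endpoint in section 8.1.2 is broad and open-ended; at 10% a doubling would usually be detected. So the figures must be given as a range. The rate could also be low: section 8.1.3 lists first-year events under other parameters, which suggests that the endpoint covers mainly months 12 to 24.
- **The 20% to 25% loss belongs to a questionnaire outcome.** Section 8.3 takes revisions from the LROI register, so 250 per arm may be fairer. At 2% to 4.6% the miss is then still 46% to 73%.
- **Separate analysis matches the sample size, and pooling does not cure imprecision.** Both true. Pooling narrows the limit; it does not make the trial large enough to exclude a small excess.
- **Section 3 provides for long-term register monitoring of revisions and mortality.** That mitigates, but it does not replace the in-trial comparison of complications.

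**Conclusion.** The concern holds in a limited form. The protocol asks a safety question, has a margin for mean PROMIS only, and fixes a per-joint analysis of complications and surgical interventions that would miss a doubling about 46% to 76% of the time at assumed control rates of 2% to 4.6%. The range rests on a two-sided 5% test, 190 to 250 patients per arm and independent patients. Ignoring clustering and period is favourable to the plan. At 1%, which is more plausible for re-operations than for all complications, the miss is about 80%; at 10% it falls to 11% to 21%.

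The documents do not support the stronger conclusion that the plan will pass off non-significance as safety. What they support is that such a result would carry little information, and that a cheap change to the stated analysis would answer the question better. The label in section 10.5 is a separate clerical contradiction with sections 8.1.1 and 8.1.2.

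**What to change.** **Section 10.2.** For any complication and for any surgical intervention, add one model pooling THA and TKA, with joint as a fixed effect, a hospital effect and a parsimonious calendar-period adjustment (for example a linear trend instead of monthly effects). From it:
- report the risk difference, COD minus RFU, with its upper one-sided 97.5% limit;
- word the safety conclusion by the largest excess that this limit still allows, and say that a non-significant result will not be taken as evidence of safety;
- keep the per-joint results alongside.

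Do not promise a particular precision. At a rate of about 2% with 380 per arm, expect a pooled limit of about +2 points without period terms and roughly +4 to +7 points with them.

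**Section 10.5.** Reconcile the status of complications with sections 8.1.1 and 8.1.2.

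**Cost.** Wording in two sections and one more model for each of the two outcomes; no new patients or data. The pooled estimate assumes a similar effect in hip and knee, and the safety conclusion becomes visibly more modest.
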